**Safety Assessment**					
Hemogram		X			X
Transaminase AST		X			X
Transaminase ALT		X			X
Alkaline Phosphatase		X			X
Total Bilirubin		X			X
Triglycerides		X			X
Total Cholesterol		X			X
Blood Urea Nitrogen (BUN)		X			X
Creatinine		X			X
Urinalysis		X			X
Uric Acid		X			X
LDH (Lactate Dehydrogenase)		X			X
Lactic Acid		X			X
Ferritin		X			X
Albumin		X			X
Iron		X			X
Electrocardiogram		X			X
Echocardiogram		X			X
**Efficacy Assessment**					
RECIST		X			X
Tumor Antigens		X			X
CA199		X			X
ACE		X			X
Metabolome		X		X	X
Microbiome Analysis		X			X
Proinflammatory Cytokines		X		X	X
Circulating DNA		X		X	X
Ketone Bodies		X		X	X
Tumor Infiltration		X			X
QLQ C-30 Quality of Life Surveys		X	X	X	X
Progression-Free Survival		X			X

For newly diagnosed acute leukemias, a total of 28 new patients will be recruited, and an additional six patients will be recruited for the relapsed leukemias group. Both groups will receive continuous treatment with the Esperanza extract at the determined MTD for four weeks. Standard chemotherapy treatment for their underlying disease will be administered to both groups. At the end of the treatment cycle, safety and efficacy evaluations will be conducted. Table 3 provides a comprehensive list of the activities to be carried out during the patients' intervention.

**Table 3 Tab3:** Activity schedule for phase II clinical trial in acute leukemias

Schedule of activities				
**Acute leukemias**				
	**Enrollment**	**Initial Visit and chemotherapy cycle 1**	**Cycle 2**	**Close-out**^**a**^
**Time point**	**Week 1**	**Week 2**	**Week 6**	**Week 10**
Enrolment				
Screening and Informed Consent	X			
Physical Examen		X	X	X
Clinical Record		X	X	X
HIV Test and Pregnancy test	X			
**Interventions**				
Medication dispensing		**X**	**X**	**X**
Follow-up visit		**X**	**X**	**X**
**Safety Assessment**				
Hemogram		X		X
Transaminase AST		X		X
Transaminase ALT		X		X
Alkaline Phosphatase		X		X
Total Bilirubin		X		X
Triglycerides		X		X
Total Cholesterol		X		X
Blood Urea Nitrogen (BUN)		X		X
Creatinine		X		X
Urinalysis		X		X
Uric Acid		X		X
LDH (Lactate Dehydrogenase)		X		X
Lactic Acid		X		X
Ferritin		X		X
Albumin		X		X
Iron		X		X
Electrocardiogram		X		X
Echocardiogram		X		X
**Efficacy Assessment**				
Myelogram and flow cytometry		X		X
Tumor Antigens		X		X
Metabolome		X		X
Microbiome Analysis		X		X
Proinflammatory Cytokines		X		X
Circulating DNA		X		X
Ketone Bodies		X		X
Tumor Infiltration		X		X
QLQ C-30 Quality of Life Surveys		X	X	X
Progression-Free Survival		X		X

^a^For new diagnosis the intervention will be only in induction chemotherapy cycle with the close out visit in week 6

The Esperanza and Placebo capsules will be manufactured at Labfarve Laboratories in strict adherence to Good Manufacturing Practices (GMP) conditions. The Esperanza capsules contain 500 mg of *P. alliacea* extract, which is obtained from freshly crushed leaves infused with purified water. The extraction process has a DER (Drug extraction ratio) of 29–44:1, and the hexose content ranges between 3.0% and 5.0%. Each batch undergoes chemical profile assessment to ensure consistency. Quality controls are conducted in accordance with regulations set forth by the World Health Organization (WHO), the National Institute for Food and Drug Surveillance (INVIMA), and the U.S. Food and Drug Administration (FDA). These controls will be applied to both the investigational phytomedicine and the placebo, guaranteeing an identical physical appearance and a shelf life of six months from the date of manufacture.

### Criteria for discontinuing or modifying allocated interventions {11b}

Each subject retains the right to voluntarily withdraw from the study treatment at any given time. Moreover, the investigator holds the authority to suspend a subject from the study treatment if deemed necessary for various reasons, such as the occurrence of adverse events or non-adherence to the study protocol. Instances where a subject may be withdrawn from the study treatment include: withdrawal of consent by the subject or their legally acceptable representative, experiencing unacceptable toxicity (grade ≥ 3) with the combination of Esperanza and standard therapy according to NCI CTCAE version 5.0, as well as cases where the investigator determines the toxicity to be clinically intolerable. Additionally, suspension may occur if there is a clinically significant elevation that falls below grade 3 or 4, at the discretion of the investigator. Significant non-compliance with the protocol that could jeopardize the subject's safety or compromise data integrity also warrants withdrawal. The investigator may also make the decision to withdraw a subject if it is believed to be in the subject's best interest. Lastly, a positive pregnancy test will result in immediate withdrawal from the study treatment.

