### Objectives {7}

The main goal of phase I is to assess the safety, toxicity, and maximum tolerated dose (MTD) of the Esperanza extract in patients diagnosed with metastatic gastric tumors and acute leukemias. In phase II, the focus shifts to evaluating the safety of the extract and examining its impact on improving patients' quality of life using the QLQ-C30 scale for gastric tumors. Additionally, in the context of acute leukemias during phase II, the emphasis remains on determining the safety of the extract and investigating its potential to enhance the rate of remission during induction therapy and/or facilitate hematological recovery.

In addition to the primary objectives, there are important secondary objectives for gastric tumors. One of these is to evaluate the influence of the Esperanza extract on progression-free survival and clinical response, which will be assessed using the RECIST 1.1 criteria. For acute leukemias, the assessment will focus on event-free survival, defined as the duration from enrolment to disease progression, including local or distant recurrence, second primary malignancy, primary malignancy-related death, or death from any cause, whichever comes first. Furthermore, a thorough evaluation of the impact on patients' quality of life will also be conducted.

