#### Newly diagnosed and/or relapsed acute leukemias:

Patients will receive standard therapy as determined by their hematologist, which may involve treatment regimens utilizing anthracyclines, nitrogenous mustards, vinca alkaloids, antimetabolites, and topoisomerase inhibitors. The specific doses will be determined by the patient's clinical hematologist in accordance with the institutional, national, and international guidelines adopted by the Hospital Universitario San Ignacio for acute leukemias. Alongside the chemotherapy protocol, antiemetic agents such as setrons and steroids, as well as fosaprepitant administered prior to infusion, may be included. Oral setrons every 12 h for approximately 5 days, proton pump inhibitors like omeprazole, and antidiarrheals such as loperamide (especially in the case of taxanes) may also be prescribed. Colony-stimulating factors such as Pegfilgastrim/Filgastrim and folic acid analogues may be utilized.

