## Assignment of interventions: allocation

### Sequence generation {16a}

During the screening visit, all participants will be assigned a unique subject number in sequential order (e.g., 001, 002, 003, etc.), which will remain consistent throughout the study. The treatment chosen by the attending physician will be administered to all participants, without randomization in phase I.

In phase II, patients with gastrointestinal tumors will undergo randomization using a specially designed application within the eCRF in RedCap®. The randomization will be conducted using a simple non-stratified approach, predetermined, and loaded into the eCRF for the pharmacist, who will be unblinded. Randomization will not be employed for acute leukemias, as the comparison of outcomes will be conducted against a historical group using propensity score matching.

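### In the phase II leukaemia cohorts, the extract's stopping ground does not separate expected chemotherapy cytopenia from possible extract toxicity, and patients who stop early are not expressly kept in the historical comparison

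*Protocol article*

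**What the plan says.** Section 11b of the Protocol article gives one list of stopping grounds for all cohorts. It opens "Instances where a subject may be withdrawn from the study treatment include", and one entry is "experiencing unacceptable toxicity", glossed as grade 3 or higher, "with the combination of Esperanza and standard therapy according to NCI CTCAE version 5.0". Attribution to the extract is not required, and haematological toxicity is not treated separately.

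The leukaemia plan presupposes marrow suppression. The phase II aim is to "enhance the rate of remission during induction therapy and/or facilitate hematological recovery" (Objectives, section 7). Concomitant care adds: "Colony-stimulating factors such as Pegfilgastrim/Filgastrim and folic acid analogues may be utilized" (section 11d).

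On exposure, the phase II treatment text says "Both groups will receive continuous treatment with the Esperanza extract at the determined MTD for four weeks", whereas Trial design (section 8) gives relapsed patients the extract during rescue cycles 1 to 3.

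On the comparison: "Randomization will not be employed for acute leukemias, as the comparison of outcomes will be conducted against a historical group using propensity score matching" (section 16a).

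On data after a stop:
- Sections 20a and 20c plan no imputation and restrict each analysis to patients with complete information, after an active search of the hospital record, the laboratory database and the patient.
- Section 12 censors patients who have not reached the evaluation time and follows them to the end of treatment.
- Table 3 lists "Progression-Free Survival" among the leukaemia assessments.

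**The concern.** Two features combine. First, grade 3 or higher cytopenia caused by induction or rescue chemotherapy alone falls within the wording of a listed stopping ground. Two haematologists could follow the text and handle identical cytopenia differently, without blinding and with no concurrent arm.

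Second, the stated analysis rules do not say that a patient who stops stays in the comparison. Those most open to a stop for cytopenia are those with the deepest or longest suppression. If they also lack close-out data and are dropped, the remaining patients look better on haematological recovery than a historical group that had no extract to stop. If they are kept, their shortened exposure cannot be told apart from lack of activity. Recording toxicity of the combination as a safety outcome is correct; the question is only its use as a stopping ground and what happens to the data afterwards.

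**Working it through.** **1. What the stopping ground covers.** It is permissive, requires the toxicity to be judged unacceptable, and withdraws the patient from study treatment, not from the study. It does refer to toxicity of the combination. Expected cytopenia is thus a possible reason to stop, not a mandated one.

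**2. How a patient could leave the analysis.** Table 3 schedules the marrow examination, flow cytometry and blood count at the initial visit and at close-out only. A patient is lost to the remission analysis if three things happen: the extract is stopped, close-out is missed, and the record search finds no assessment. For newly diagnosed patients, dosing starts in week 2 and close-out is in week 6, so a patient stopped on day 14 needs about two more weeks of observation. The documents give no rate for any of the three steps.

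**3. Effect on the remission rate if patients are lost.** Let s be the share lost, r1 the remission rate in those kept and r0 in those lost.

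Full-cohort rate = (1 − s)·r1 + s·r0; complete-case rate = r1; difference = s·(r1 − r0).

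With an assumed r1 − r0 of 0.20:
- s = 3/28 = 0.107: 2.1 percentage points
- s = 0.25: 5 points
- s = 0.50: 10 points

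Without assuming r0, m lost patients leave the rate undetermined over a width of m/28: 3.6 points for one, 10.7 for three, 17.9 for five. These are illustrations, not forecasts.

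**4. Sample size and power.** Section 14 gives ANOVA, effect size 0.4, alpha 0.05, beta 0.20 and n = 28. For two groups, f = 0.4 means d = 0.8, and n = 2(1.960 + 0.842)²/0.8² = 24.5, so 25 per group; 25/0.9 = 27.8, so 28. (The exact F-test gives 26 per group before any allowance.) The figure reproduces as the size of the treated group and may already contain a 10% allowance, although one is stated only for gastrointestinal tumours.

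Power by two-group t-test, two-sided 0.05:
- 28 v 28: 0.836
- three matched pairs lost, 25 v 25: 0.791
- five treated patients lost, all 28 controls kept, 23 v 28: 0.796
- 2:1 matching, nine sets lost, 19 v 38: 0.799

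The loss that brings power just under 80% ranges from 11% to 32% according to a matching ratio the article does not state. The calculation also treats the outcome as continuous, whereas remission is binary. With no stopping rate either, no power loss can be assigned to this rule.

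**5. Survival follow-up.** Suppose treatment in section 12 means the extract, and the one month of monitoring in section 30 runs from the last dose. Follow-up from first dose is then stop day + 30, against about 91 days for the 3-month evaluation:
- day 28: 58 days, 33 short
- day 14: 44 days, 47 short, of which 14 are due to the stop
- day 7: 37 days, 54 short, of which 21 are due to the stop

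Most of the shortfall exists after a full four-week course. It comes from the section 12 follow-up limit more than from the stopping ground.

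**The case against.** The strongest reply is that nothing forces the harm. A haematologist need not call expected cytopenia unacceptable, and the text only allows a stop. A reader might infer that grade 3 cytopenia obliges withdrawal; the wording does not support that.

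Counting toxicity of the combination is also defensible. Safety is a primary aim, and without a concurrent arm prolonged suppression cannot readily be attributed to chemotherapy rather than to the extract or an interaction. This stands, and it is why delayed recovery must remain a stopping ground.

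A reader might further infer that data after a stop are simply lost. That is too strong. Evaluations are scheduled for all participants (section 18a), missed visits are pursued (18b), telephone contact is weekly (11c), monitoring runs one month after treatment (30), and records are searched at the single hospital where patients are treated. But sections 20a and 20c still exclude anyone whose data remain incomplete.

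The follow-up limit is less clear for leukaemia than for gastrointestinal tumours. Section 12 counts progression-free survival from randomisation, which leukaemia patients do not undergo, while Objectives defines event-free survival from enrolment with no such limit.

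Finally, an article condenses a fuller protocol, which may define toxicity handling and analysis sets. That excuses omissions, but the complete-case and follow-up rules are stated here.

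**Conclusion.** The concern holds in a limited form. The stopping ground is a modest clarification: permissive wording that does not separate expected cytopenia from possible extract toxicity. The stronger part is the pairing of a stated complete-case rule with follow-up limited to the end of treatment, in a non-randomised comparison with historical patients. Together they leave early stoppers not expressly retained.

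The size cannot be determined from the documents. The remission-rate illustrations assume a loss share and a difference between lost and retained patients; the follow-up figures assume what treatment means and when the month of monitoring starts. A reader might infer an underpowered comparison from the small number of losses that takes power below 80%, but those figures rest on an assumed loss and matching ratio and are not an effect of this rule.

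**What to change.** 1. **Sections 20a and 20c, leukaemia cohorts:** analyse every patient who took at least one dose. Obtain outcomes from the record search already planned when close-out is missed, and count patients with no remission assessment as not in remission. This convention errs against the extract.
2. **Section 12:** continue scheduled assessments and survival follow-up to the planned time point whether or not the extract was stopped.
3. **Section 11b, leukaemia cohorts:** state that expected cytopenia from induction or rescue chemotherapy is not by itself a ground to stop the extract during its planned exposure. Define that exposure as induction for new diagnoses and the rescue cycles for relapsed patients, since a fixed four weeks does not fit the latter. Keep as grounds intolerable toxicity, recovery delayed beyond what the haematologist expects, and the patient's best interest.

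The cost is wording. No visits, samples or patients are added, and relationship to the study drug is already recorded for each adverse event (section 22). The downside is a little more follow-up from hospital records and slightly less explicit haematological stopping protection, offset by the grounds that remain.

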### Strategies to improve adherence to interventions {11c}

All participants are scheduled for regular follow-up visits, during which a medication count is conducted to assess adherence rates. In addition, participants can address any questions they may have, and the evaluation of adverse effects that occurred during the intervention is performed. Furthermore, a telephone follow-up is carried out weekly, ensuring that participants can directly contact the coordinator to seek clarification, resolve doubts, or report any abnormal clinical signs they may be experiencing.

### Relevant concomitant care permitted or prohibited during the trial {11d}

#### Metastatic gastrointestinal tumors:

Patients will receive standard therapy as determined by their oncologist, which may involve treatment regimens incorporating platinums, topoisomerase inhibitors, fluoropyrimidines, or antimetabolites. The specific doses will be determined by the patient's clinical oncologist in accordance with the institutional, national, and international guidelines adopted by the Hospital Universitario San Ignacio for metastatic gastrointestinal tumors. In addition to the chemotherapy protocol, antiemetic agents such as setrons and steroids, as well as fosaprepitant administered prior to infusion, may be included. Oral setrons every 12 h for approximately 5 days, proton pump inhibitors like omeprazole, and antidiarrheals such as loperamide (especially in the case of taxanes) may also be prescribed. Colony-stimulating factors such as Pegfilgastrim and folic acid analogues may be utilized.

#### Newly diagnosed and/or relapsed acute leukemias:

Patients will receive standard therapy as determined by their hematologist, which may involve treatment regimens utilizing anthracyclines, nitrogenous mustards, vinca alkaloids, antimetabolites, and topoisomerase inhibitors. The specific doses will be determined by the patient's clinical hematologist in accordance with the institutional, national, and international guidelines adopted by the Hospital Universitario San Ignacio for acute leukemias. Alongside the chemotherapy protocol, antiemetic agents such as setrons and steroids, as well as fosaprepitant administered prior to infusion, may be included. Oral setrons every 12 h for approximately 5 days, proton pump inhibitors like omeprazole, and antidiarrheals such as loperamide (especially in the case of taxanes) may also be prescribed. Colony-stimulating factors such as Pegfilgastrim/Filgastrim and folic acid analogues may be utilized.

### Provisions for post-trial care {30}

All participants will be monitored for a period of 1 month following the completion of their treatment. Additionally, after their final visit, participants will be informed that they have the option to seek clarification or report any new signs or symptoms through telephone or in-person consultations. Furthermore, patients will continue to receive regular clinical follow-up for their underlying disease, adhering to the established schemes and protocols at the Hospital.

### Outcomes {12}

The primary outcome of this study is to determine the safety, efficacy, and maximum tolerated dose (MTD) of the administration of the Esperanza extract in patients with metastatic gastrointestinal tumors as well as in patients with acute leukemias. Additionally, the study aims to assess the impact of the Esperanza extract on the quality of life of these patients using the QLQ-C30 scale. The evaluation period will be between 4 and 6 months, and the QLQ-C30 version 3 scale will be employed as the standardized method for assessing the patients' quality of life outcomes.

The secondary outcomes of this study are as follows:To determine the effect of treatment with the Esperanza extract in combination with chemotherapy on the clinical and pathological response. This evaluation will be conducted between 1 and 3 months using the Recist 1.1 (Response Evaluation Criteria In Solid Tumors) scale as the standardized evaluation method and with flow cytometry and myelogram in acute leukemias.To assess the impact of treatment with the Esperanza extract in combination with chemotherapy on the number and size of metastases. This assessment will also be carried out between 1 and 6 months, utilizing the Recist 1.1 for gastrointestinal tumors and cytometry and myelogram for acute leukemias.To determine progression-free survival and overall survival. The evaluation period for progression-free survival will be 3 months, and the Log Rank test will be used as the evaluation method. Progression-free survival will be measured from randomization to the occurrence of disease progression, local or distant recurrence, development of a second primary malignancy, or death from any cause, whichever occurs first. Patients who do not meet the evaluation time point will be censored and followed up until the end of treatment for survival curve preparation.

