**Fig. 2 Fig2:**
[figure not shown]
Comprehensive Flow Diagram for Phase II PA001 Trial **a**) Gastrointestinal Tumors, **b**) New diagnosis Acute Leukemias, and **c**) Relapsed Acute Leukemias

Conversely, in the acute leukemia group, the MTD will be administered to patients during the induction cycle. The results from these acute leukemia cohorts will be compared to a historical cohort at the hospital, allowing for further analysis and evaluation (Fig. 2b). In relapse acute leukemia patients, the MTD will be administered to patients during the rescue cycles 1 to 3, the results will be compared to a historical cohort at the hospital (Fig. 2c).

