#### Phase II treatment:

For patients with metastatic gastrointestinal tumors (colon, pancreas, stomach, and bile ducts), a total of 30 new patients will be enrolled and divided into two groups: an intervention group and a placebo group, each consisting of 15 patients. The intervention group will receive continuous treatment with the Esperanza extract at the determined maximum tolerated dose (MTD) for three treatment cycles, equivalent to approximately 12 weeks. The placebo group will receive a placebo in addition to standard chemotherapy treatment for their underlying disease. Safety evaluations will be conducted at the end of each treatment cycle, and the efficacy evaluation will be carried out after completion of the three treatment cycles. Table 2 provides a comprehensive list of the activities to be carried out during the patients' intervention.

**Table 2 Tab2:** Activity schedule for phase II clinical trial in gastrointestinal tumors

Schedule of activities					

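### Newly diagnosed leukaemia closes out at Week 6, so the 3-month PFS that the protocol schedules for it is not observed, and EFS and OS have no stated follow-up horizon

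*Protocol article*

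**What the plan says.** All statements are in the protocol article.

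- **Endpoint and horizon (Outcomes {12}).** PFS and OS are secondary outcomes. "The evaluation period for progression-free survival will be 3 months, and the Log Rank test will be used as the evaluation method". PFS is timed from randomization. Patients who do not reach the evaluation time point are "censored and followed up until the end of treatment for survival curve preparation". No evaluation period is given for OS.
- **Leukaemia objective (Objectives {7}).** "For acute leukemias, the assessment will focus on event-free survival", counted from enrolment, with no time horizon.
- **Leukaemia schedule (Table 3).** Enrolment is Week 1, the initial visit Week 2 and close-out Week 10. PFS, myelogram and flow cytometry are marked at the initial visit and close-out only. The footnote changes this for one group: "For new diagnosis the intervention will be only in induction chemotherapy cycle with the close out visit in week 6".
- **Leukaemia treatment.** The phase II treatment section covers 28 newly diagnosed and 6 relapsed patients: "Both groups will receive continuous treatment with the Esperanza extract at the determined MTD for four weeks". The Trial design section says otherwise for relapse: "In relapse acute leukemia patients, the MTD will be administered to patients during the rescue cycles 1 to 3". These two statements must be reconciled.
- **Later follow-up (Provisions for post-trial care {30}).** "All participants will be monitored for a period of 1 month following the completion of their treatment". Patients then stay in routine care at the hospital.
- **Comparator (Sequence generation {16a}).** Leukaemia patients are not randomized. They are compared with a historical group by propensity score matching.
- **Gastrointestinal group (Phase II treatment, Table 2).** Treatment runs "for three treatment cycles, equivalent to approximately 12 weeks". RECIST and PFS are marked at the initial visit and at close-out in Week 12–14.

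**The concern.** The protocol names a time-to-event outcome with a 3-month evaluation, schedules it for leukaemia, and closes most of those patients out well before 3 months. The only sentence on survival-curve follow-up for patients who miss the time point stops at the end of treatment, which is four weeks here. The definition also starts the clock at randomization, an event that leukaemia patients never have.

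At stake is what the leukaemia survival results can mean. A curve or log-rank test labelled as 3-month PFS, or as EFS with no horizon, would describe little beyond induction. No common cut-off is stated for the historical records. If those records run longer, the later part of the plotted curves would rest on controls alone, and matching on baseline factors does not change that.

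**Working it through.** The protocol gives no event count, hazard ratio or power for PFS, EFS or OS, so there is no survival figure to reproduce. The check is calendar arithmetic with 1 month = 365.25/12/7 = 4.35 weeks, so 3 months = 13.04 weeks. The leukaemia time origin is not settled, so both Week 1 (enrolment) and Week 2 (initial visit) are used.

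**1. Weeks observed**

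| Group | Close-out | Weeks to close-out (from Week 2 / Week 1) | With 1 month more | Needed |
|---|---|---|---|---|
| Newly diagnosed leukaemia | Week 6 | 4 / 5 | 8.3 / 9.3 | 13.0 |
| Relapsed leukaemia | Week 10 | 8 / 9 | 12.3 / 13.3 | 13.0 |
| Gastrointestinal | Week 12–14 | 10–12 / 11–13 | 14.3–16.3 / 15.3–17.3 | 13.0 |

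For newly diagnosed leukaemia, monitoring ends at Week 6 + 4.35 = Week 10.3. Three months falls at Week 1 + 13.04 = Week 14.0, or Week 2 + 13.04 = Week 15.0. The gap is 8 to 9 weeks after close-out and about 4 to 5 weeks after monitoring ends. Relapsed leukaemia is borderline if Table 3's Week 10 applies. The gastrointestinal close-out lies at about the 3-month mark, and the extra month passes it.

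**2. Share of 3-month events captured in newly diagnosed leukaemia**

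The protocol gives no event rate. Assume a constant hazard with median M, so that F(t) = 1 − 0.5^(t/M), with M in weeks. The share is F(t)/F(13.04), counted from Week 2.

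- M = 3 months: F(4) = 0.192, F(8.35) = 0.358, F(13.04) = 0.500. The shares are 38% by close-out and 72% by the end of the extra month.
- M = 24 months: F(4) = 0.0262, F(8.35) = 0.0539, F(13.04) = 0.0830. The shares are 32% and 65%.

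Both shares are cumulative. Counting from Week 1 instead (5 and 9.35 weeks), they are 39–47% and 72–78%.

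**3. Expected events among the 28 patients, 28 × F(t)**

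| Assumed median | By Week 6 | With 1 month more | At 3 months |
|---|---|---|---|
| 3 months | 5.4 | 10.0 | 14.0 |
| 6 months | 2.8 | 5.6 | 8.2 |
| 12 months | 1.4 | 2.9 | 4.5 |

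**4. Gastrointestinal progression dates**

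Table 2 has one post-baseline RECIST assessment, at Week 12–14. Progressions found on that scan share nearly one date, so a log-rank test adds little to a comparison of the proportion progression-free at that visit.

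**The case against.** The strongest reply is that 3-month PFS was meant only for the gastrointestinal group. Objectives {7} assigns PFS there and EFS to leukaemia, and only those patients are randomized. The censoring sentence covers only patients who miss the time point, and the one-month limit stands under post-trial care, not in an OS rule. Other windows are longer: Outcomes {12} allows cytometry and myelogram between 1 and 6 months. A condensed article may also leave OS follow-up to the full protocol.

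Part of this stands. OS follow-up is unspecified, not shown to stop at one month. The intended reading of PFS does not remove the conflict, however, because Table 3 marks PFS for leukaemia and EFS has nearly the same events. The 1-to-6-month window adds a further mismatch, since Table 3 has no visit after Week 10.

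Four stronger readings are tempting, and the documents do not support them:

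- **PFS cannot be answered anywhere in the trial.** The gastrointestinal close-out falls at about 3 months, and relapsed leukaemia is borderline.
- **Early EFS is only induction death.** The definition includes progression, and progression or refractory disease can be seen on the Week 6 marrow.
- **Unequal follow-up would produce a false finding of no difference.** Under non-informative administrative censoring, the log-rank test uses times when both groups are at risk. The comparison is confined to early events and loses precision. The protocol does not say how long the historical records run.
- **One gastrointestinal scan biases the comparison.** Both blinded arms share the schedule, and routine scans are not excluded. The cost is timing information.

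**Conclusion.** The conflict is real for newly diagnosed leukaemia, 28 of the 34 phase II leukaemia patients. Observation is 4 to 5 weeks to close-out, or 8.3 to 9.3 weeks with the monitoring month, against 13.0 weeks for the stated evaluation. This rests on the protocol's own calendar. The captured shares in the working illustrate the loss and depend on the assumed constant hazard and medians.

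EFS can still be estimated, but only for about the first 4 to 9 weeks, and the historical comparison is restricted in the same way. The PFS time origin does not exist for leukaemia, and OS has no horizon. The gastrointestinal single-scan issue is a secondary efficiency point.

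This should be fixed but is not critical. The outcomes are secondary, the sample sizes rest on quality of life and response, and the Discussion leaves efficacy to later phase III trials.

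**What to change.** 1. Replace the end-of-treatment follow-up clause in Outcomes {12} with one stated cut-off for progression, relapse and vital status, at least 3 months from a defined start. For leukaemia, define that start as enrolment or treatment start in place of randomization. State the OS and EFS horizons.
2. Collect these data by chart abstraction from SAHI, which the statistical section already names for retrieving missing data. Patients remain in routine follow-up at the hospital.
3. Censor the historical controls at the same cut-off, counted from the matching start.
4. If follow-up is not extended, report leukaemia outcomes as status at close-out, and drop leukaemia PFS, EFS and OS as time-to-event outcomes.
5. For gastrointestinal PFS, if only the two Table 2 scans are used, report the proportion alive and progression-free at close-out as the main summary.

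The cost is a wording change, one later chart abstraction per patient and somewhat later survival reporting. No visits or scans are added.
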